### Statistical Analysis Plan

The study’s primary outcome is PPGR. Following the Wolever and Jenkins method [31], as adapted by Zeevi et al [18], Mendes-Soares et al [20], and Berry et al [32], logged meal times and continuous glucose measurements will be used to calculate the incremental area under the curve. Before conducting analyses, meals logged less than 30 minutes apart will be merged and meals logged within 90 minutes of other meals will be removed. Meals that are very small (<15 g and <70 calories), very large (>1 kg), with implausibly low PPGR values (ie, a PPGR < 5 mg/dL·h after consuming ≥ 40 g of carbohydrates), that are incompletely logged, and which are consumed in the first and last 12 hours of the CGM connection will also be removed. To reduce noise, the median of all glucose values from the 30-minute period before the meal will be taken as the initial glucose level, above which the incremental area will be calculated. Meals that had incomplete glucose measurements in the time window of 30 minutes before and 2 hours after the logged mealtime will be filtered out.

Descriptive statistics will be used to plot the range of PPGRs responses to standardized test meals as well as the correlation between PPGR and the nutritional composition of the logged meals (ie, carbohydrates, fat, and protein).

A machine learning predictor will be developed based on stochastic gradient boosting regression (XGBoost, version 2.2.1; The XG Boost Contributors) [33] using the XGBRegressor class. PPGR will be predicted as the sum of predictions from thousands of decision trees. Trees will be inferred sequentially, with each trained on the residual of all previous trees. The features incorporated in each tree are selected by an inference procedure from features representing meal content (ie, calorie, protein, carbohydrate, and fiber content), meal timing, baseline demographics (ie, age, sex, predominant diet, health conditions, family history, and current medications), baseline survey results (ie, WHO STEPS, WHO-5, Diabetes Distress School, Wilson Adherence Scale, and Pittsburgh Sleep Quality), baseline biometric values (ie, blood pressure, heart rate, weight, height, and body measurements at the upper arm, thigh, calf, waist, and hips), baseline laboratory values (complete blood count, HbA_1c_, blood electrolytes, creatinine, cholesterol, and urinalysis), as well as CGM, heart rate, and activity data.

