Performance will be assessed by holding out 30% of the sample and using 5-fold cross-validation in which cross-validation participants are divided into 5 groups, the model will be trained on the other 4 parts. Random datasets of the same size as the original will be sampled with replacement from the original dataset, and the entire training and validation process will be repeated. The performance will be measured by the ability to accurately predict meals reported by the held-out participants. Prediction results will be aggregated, and Pearson product moment correlation with the measured PPGRs will be reported. The SE for the calculated performance will be assessed using at least a thousand iterations of bootstrapping until the errors stabilize. Model discrimination will be assessed using a binary cut-point for PPGR, set at the 50th percentile of all observed PPGR values, plotting a receiver operating characteristic curve (ROC) and then calculating the area under the ROC.

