## Discussion

### Study Implications

This study will provide the first large scale examination of variability in blood glucose responses to food in India and will be among the first to estimate PPGR variability for individuals with T2D in any jurisdiction. We hypothesize that there will be substantial interindividual variability in PPGR and that, based on the data collected from this study, machine learning models will be able to accurately predict individual PPGR responses. This will facilitate the prescription of truly personalized diets for individuals with T2D.

These results will be particularly important in the context of the rapidly rising prevalence of T2D in India [34]. Along with medications and physical activity, diet is a key tenant of effective blood glucose control [15]. Like in other jurisdictions, guidelines call for individualization of meal planning, which is sometimes referred to as “Medical Nutritional Therapy.” Despite this, personalization of dietary plans are generally based upon broad constructs like age, activity level, health status, and preferences, and, for all patients, tend to emphasize overall calorie reductions and minimization of carbohydrate [16]. especially added sugars and refined grains, in favor of the consumption of nonstarchy vegetables and foods that are high in protein [35].

However, emerging data demonstrates that there are marked interindividual responses to food [17], attributed to differences in physical activity [36], gut microbiome [18,19,37], and genetics [38], including in variations in skeletal glucose transporters related to insulin resistance [39]. For example, a study conducted in the United States among nondiabetic individuals with a mean BMI of 27 found PPGR to a standardized meal of bagel and cream cheese ranged from 6 to 94 mg/dL·h [20]. A similar study conducted in Israel enrolled nondiabetic individuals of whom 3-quarters had a BMI ≥ 25 and found mean PPGR to bread and butter of 44 mg/dL·h but the bottom decile had responses of ≤ 15 mg/dL·h and the top decile has responses ≥ 79 mg/dL·h [18]. Similar data have been generated for individual without diabetes in the United Kingdom and the United States [19,20], and for individuals with type 1 diabetes in Israel [40].

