There is exceptionally limited data for variability in PPGR for individuals with T2D in the peer-reviewed although it is highly likely that such variability exists [22]. The primary goal of our study is to fill this void and to generate an India-specific machine-learning models on the basis of which PPGR can be predicted with high accuracy for T2D. Similar models have been built in other jurisdictions. For example, a machine learning algorithm trained on CGM data, dietary, activity, anthropometrics, and gut microbiota for nondiabetic individuals in Israel was much more accurate at predicting PPGR than generic models based on the carbohydrate content or the amount of calories in a meal [18]. A separate US-based study had similar findings [20].

Among individuals with diabetes, a study in the Netherlands that included a small number of individuals with T2D along with individuals with prediabetes and normal glucose metabolism, a machine learning model based on CGM data was highly accurate in predicting future glucose values but this study did not specifically evaluate the ability to predict PPGR [41]. A US study of 1000 patients of whom 1-quarter had T2D found that a machine learning model trained on CGM, HRM data and food logs was highly accurate at predicting PPGR but this study has, to our knowledge, only been published in abstract form [22]. These studies have all relied on CGM data to make their predictions. While these devices are increasingly used, practice guidelines do not recommend their long-term use for most individuals with T2D [42]. Accordingly, a key goal of our study will be to explore the ability to predict PPGR response without reliance on CGM data or with very limited blood glucose data from patients.

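### The predictor is evaluated only by its own r and AUC, with no meal-only reference model, so the planned metrics cannot show that personal features add anything

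*Protocol article*

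**What the plan says.** The Statistical Analysis Plan section of the protocol article describes a single gradient-boosting model. Its inputs start with "features representing meal content (ie, calorie, protein, carbohydrate, and fiber content), meal timing, baseline demographics" and go on to surveys, biometrics, laboratory values, and CGM, heart rate and activity data.

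The outcome is the 2-hour incremental area above a baseline taken from the same sensor: "the median of all glucose values from the 30-minute period before the meal will be taken as the initial glucose level".

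The evaluation is set out in some detail:
- Split: "Performance will be assessed by holding out 30% of the sample and using 5-fold cross-validation".
- Target: "The performance will be measured by the ability to accurately predict meals reported by the held-out participants".
- Main output: "Prediction results will be aggregated, and Pearson product moment correlation with the measured PPGRs will be reported", with a bootstrap standard error.
- Second output: "Model discrimination will be assessed using a binary cut-point for PPGR, set at the 50th percentile of all observed PPGR values", followed by the area under the ROC curve.

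Neither this section nor Sample Size Considerations names a reference model, a nested model or a measure of incremental performance. The same section does plan a descriptive correlation of PPGR with the carbohydrate, fat and protein content of logged meals.

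Sample Size Considerations gives the design purpose as predicting PPGR from individual characteristics. Study Implications, in the Discussion, hypothesizes that "machine learning models will be able to accurately predict individual PPGR responses" and that this will lead to personalized diets. The Discussion credits an earlier predictor because it "was much more accurate at predicting PPGR than generic models based on the carbohydrate content or the amount of calories in a meal". It also names prediction with little or no CGM data as a key goal.

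**The concern.** The study's purpose is a claim about added value: knowing the person should improve on knowing the meal. The two planned metrics measure something else, namely how well everything together predicts PPGR. Because meal content and personal features enter one model, a high r or AUC does not show which of them produced it.

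There is a second non-personal route to a good score. PPGR is measured above pre-meal CGM glucose, and CGM data are also predictors. A transiently low pre-meal value tends to enlarge the measured increment and can itself be used to predict it. Some correlation then arises from regression to the mean, even if food acts identically on everyone.

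What is at stake is how the predictor result is read. The article itself presents beating carbohydrate and calorie models as the achievement of earlier work, yet its plan contains no comparison that could show the same here.

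**Working it through.** **Inputs from the article (Sample Size Considerations; Statistical Analysis Plan).** 1000 evaluable participants × 14 days × 3 meals = 42,000 meals, as stated. Reading the 30% hold-out as participants gives 300 people and 300 × 42 = 12,600 meals.

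**The plan's own power figure.** For r = 0.13, n = 1000, two-sided P<.005: atanh(0.13) × √997 − 2.807 = 0.1307 × 31.58 − 2.807 = 1.32, so power is 90.7%. This agrees with the stated figure of more than 80%. It concerns a correlation differing from zero, not a gain over a reference model, so it does not bear on this point.

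**Check 1: score of carbohydrate alone.** The share of PPGR variance explained by carbohydrate (R²) is not in the article; 5% to 25% is assumed. Personal features are given no effect. For a linear predictor r = √R². Under bivariate normality the AUC at a median split is 0.5 + (2/π) × arcsin(r/√2).

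| Assumed R² | r | AUC |
|---|---|---|
| 5% | 0.22 | 0.60 |
| 10% | 0.32 | 0.64 |
| 15% | 0.39 | 0.68 |
| 20% | 0.45 | 0.70 |
| 25% | 0.50 | 0.73 |

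A simulation with 1000 people × 42 meals, 300 people held out, and an unpredictable person effect making up 30% of residual variance gave the same values to within 0.01. The SD of r across replicates was 0.008 to 0.009.

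**Check 2: full model with useless personal features.** Same design, with 30 irrelevant personal features added to carbohydrate and a linear model standing in for XGBoost. Held-out results:

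| Assumed carbohydrate–PPGR correlation | Full model r | Carbohydrate-only r | Full model AUC | Carbohydrate-only AUC |
|---|---|---|---|---|
| 0.2 | 0.19 | 0.20 | 0.59 | 0.59 |
| 0.3 | 0.28 | 0.29 | 0.63 | 0.63 |
| 0.4 | 0.38 | 0.39 | 0.68 | 0.68 |
| 0.5 | 0.50 | 0.50 | 0.73 | 0.73 |
| 0.6 | 0.59 | 0.60 | 0.77 | 0.78 |

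The planned metrics rise to 0.59 and 0.77 while the gain over carbohydrate is zero or slightly negative.

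**Check 3: shared baseline.** Every meal and person was given the same food response. Assumed inputs: within-person glucose wander with SD 20 to 30 mg/dL and correlation time 2 to 8 hours, between-person SD 35 mg/dL, sensor noise SD 5 mg/dL, readings every 5 minutes. Pre-meal glucose alone gave r of about 0.15 to 0.35 (AUC 0.57 to 0.66). Its deviation from the person's usual level gave r of about 0.30 to 0.54 (AUC 0.64 to 0.75). The exclusion of meals with implausibly low PPGR was not modelled.

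**Check 4: what a pooled gain would show.** Suppose carbohydrate explains 15% of variance and a baseline characteristic explains another 15% purely as a shift in each person's level. Pooled r rises from √0.15 = 0.39 to √0.30 = 0.55. Within person, both models give √(0.15/0.85) = 0.42, because the shift cancels once meals are centred on the person's mean. Everyone still ranks meals identically, so a pooled gain alone would not support personalized diets.

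**The case against.** Several objections have force.

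- **No success rule exists.** The article states no threshold and no test against zero. A reader might infer that the plan would declare success whatever the personal features do, or that it tests r against 0 and AUC against 0.5. The text supports neither reading. What stands is that a favourable value could be reported without evidence of personal added value.
- **A carbohydrate benchmark is partly there.** A one-variable linear model has the same absolute r as the planned descriptive correlation with carbohydrate, so it would be too strong to say that readers get no benchmark. However, that correlation is not tied to held-out participants, gives no AUC, omits calories and pre-meal glucose, and is not compared with the model.
- **A no-CGM model is a stated goal.** It would remove much of the shared-baseline route. It would still mix meal and personal features, so it is not a meal-only reference.
- **The sizes depend on assumptions.** This is correct, and they are given as ranges. The larger shared-baseline figures also need a feature built as deviation from the person's usual level, which the article does not name.
- **This may be left to a fuller plan.** An analysis plan that is not shown may name benchmarks, and the remark about earlier models commits this study to nothing. But the article fixes its performance outputs in detail, and the outputs it fixes do not address the purpose it states.

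A reader might also infer that the study's whole conclusion is at risk. It is not: the description of PPGR variability does not depend on the predictor.

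**Conclusion.** The point holds in a limited form. Pooled held-out r and median-split AUC of one mixed model cannot show whether personal features contribute, although prediction from individual characteristics and personalized diets are the stated purpose. Carbohydrate alone would give r of about 0.22 to 0.50 and AUC of about 0.60 to 0.73 if it explains 5% to 25% of PPGR variance. That range is assumed, and the results also rest on a linear carbohydrate effect and roughly normal variables. The shared baseline could add correlation of its own, of a size that depends on assumed glucose fluctuation. Nothing here shows that personal features will fail to help, or that the planned metrics are wrongly computed. The change is worth making before results are seen.

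**What to change.** In the Statistical Analysis Plan section, add reference models fitted and evaluated on the same participant-level splits:

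- (a) carbohydrate only, and calories only;
- (b) meal content plus meal timing;
- (c) meal content plus meal timing plus pre-meal glucose.

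Report their held-out r and AUC beside those of the full model and of the no-CGM model named in the Discussion. Report the gain in r and AUC with bootstrap intervals that resample participants. Treat (c) as a diagnostic for the shared-baseline artefact. It is not a purely non-personal reference, because pre-meal glucose differs between people and a gain over (c) discounts some genuine individual information.

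Also report the gain in within-person r, with meals centred on each participant's mean. Base statements about individual prediction on the gain over the meal-only models, and statements about personalized diets on the within-person gain, rather than on the full model's r or AUC alone.

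The cost is revised wording and a few extra fits on data already being collected, with no new participants. The headline result becomes a smaller increment.

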### Sample Size Considerations

A total of 1050 individuals will be targeted for recruitment. Assuming a 5% loss to follow-up, this corresponds to 1000 evaluable individuals at the end of the study. The study has been designed to predict postprandial glucose responses based on individual characteristics and 1000 participants followed for 14-days will result more than 4 million glucose readings (assuming glucose readings from the CGMs every 5 minutes) and 42,000 meals (assuming 3 meals per participant per day). This volume of data will also provide more than 80% power to detect correlations of a magnitude of *r*=0.13 (*R*^2^=0.02) with *P*<.005. We will also be sufficiently powered to detect effects of *r*=0.17 (*R*^2^=0.03, ie, explaining 2.7% of interindividual variation) with *P*<.001, that is, accounting for 5000 independent hypothesis tests.

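### A pooled Pearson correlation and an AUC at the overall median cannot, on their own, support claims of accurate individual prediction or of personalized diets

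*Protocol article*

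**What the plan says.** In the protocol article, Methods, Statistical Analysis Plan, the evaluation is described as follows.

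- Validation: "Performance will be assessed by holding out 30% of the sample", together with 5-fold cross-validation by participant groups.
- Target: "The performance will be measured by the ability to accurately predict meals reported by the held-out participants".
- First measure: "Prediction results will be aggregated, and Pearson product moment correlation with the measured PPGRs will be reported", with a bootstrap standard error.
- Second measure, presented as discrimination: area under the ROC curve, with PPGR dichotomized at a cut-point "set at the 50th percentile of all observed PPGR values".
- Separately, a descriptive correlation of PPGR with the carbohydrate, fat and protein content of logged meals.

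The Discussion (Study Implications) hypothesizes that "machine learning models will be able to accurately predict individual PPGR responses" and presents this as the route to personalized diets. It supports the approach with an earlier model in nondiabetic people that "was much more accurate at predicting PPGR than generic models based on the carbohydrate content or the amount of calories in a meal".

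**The concern.** The stated target is accuracy, and the stated use is choosing foods for an individual. The two measures fit neither well.

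1. **Accuracy.** Pearson r and the AUC are unchanged by any positive linear transformation of the predictions. A model could be badly off in mg/dL·h and score the same as a calibrated one.
2. **Within-person ranking.** Taken over all held-out people and meals, r rewards a model for separating high responders from low responders. The AUC does the same, because its cut-point is one value for everyone. The feature list contains many person-level variables (demographics, surveys, anthropometry, laboratory values, medications), so this part of the score could be large.
3. **Benchmark.** A model that ranks meals by carbohydrate alone can show within-person skill while giving everyone the same advice. Showing that the machine-learning model adds something therefore requires comparing the two on the same held-out meals. No such comparison is stated.

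At stake is the headline conclusion. The study could report that individual prediction is accurate, and personalized diets feasible, from figures that do not show either.

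**Working it through.** **The plan's own correlation figure.** The only performance-like number in the article is the power statement in Sample Size Considerations: more than 80% power for r = 0.13 at P<.005. By Fisher's z with n = 1000 ("this corresponds to 1000 evaluable individuals at the end of the study"), two-sided:

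- r = 0.13: atanh(0.13) × √997 − 2.807 = 4.128 − 2.807 = 1.321, power 90.7%.
- r = 0.17 at P<.001: 5.420 − 3.291 = 2.130, power 98.3%.

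The statement is reproduced. It concerns detecting an association. It sets no target for model performance, and the point here does not depend on it.

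**Inputs for the check.** 30% of 1000 participants is about 300 held out, if the split is by participant. 42,000 / 1000 = 42 planned meals each, before exclusions. The share of PPGR variance lying between people (ICC) is not given, so 0.1 to 0.6 is assumed. *Aggregated* is not defined. Pooling over people and meals is the natural reading, and no per-person correlation is mentioned.

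**Check 1: pooled r with no within-person skill.** If the predictions vary only between people, then pooled r = √(ICC × share of between-person variance captured). AUC values are simulated (300 people × 42 meals, 30 repetitions) for the model that knows each person's level.

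| ICC | r, half captured | r, all captured | AUC, all captured | Within-person r |
|---|---|---|---|---|
| 0.1 | √0.05 = 0.22 | √0.1 = 0.32 | 0.64 | 0 |
| 0.3 | √0.15 = 0.39 | √0.3 = 0.55 | 0.76 | 0 |
| 0.4 | √0.20 = 0.45 | √0.4 = 0.63 | 0.79 | 0 |
| 0.5 | √0.25 = 0.50 | √0.5 = 0.71 | 0.84 | 0 |
| 0.6 | √0.30 = 0.55 | √0.6 = 0.77 | 0.87 | 0 |

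The simulated pooled r agreed with the formula (0.31, 0.55, 0.63, 0.71 and 0.77 when all is captured), and the simulated mean within-person r was zero to two decimals.

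**Check 2: models with some skill at both levels.** For predictions calibrated at both levels, pooled r² = ICC × r_B² + (1 − ICC) × r_W², where r_B and r_W are the between- and within-person correlations. At ICC 0.5, a pooled r of 0.50 requires only r_B² + r_W² = 0.25 / 0.5 = 0.5. The same pooled r therefore fits r_W = 0 (r_B² = 0.5), r_W = 0.50 (r_B² = 0.25) and r_W = √0.5 = 0.71 (r_B = 0). Pooled r cannot tell these apart.

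**Check 3: calibration.** For scale only, take the nondiabetic bread-and-butter figures cited in the Discussion: mean 44, bottom decile at most 15, top decile at least 79 mg/dL·h. A normal approximation gives SD = (79 − 15) / (2 × 1.2816) = 25.0. Simulated predictions p with r of about 0.7:

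| Predictions | r | AUC | Bias | RMSE | Calibration slope |
|---|---|---|---|---|---|
| Calibrated, p | 0.70 | 0.83 | 0.1 | 17.9 | 1.0 |
| 0.5 × p | 0.70 | 0.83 | −21.9 | 29.6 | 2.0 |
| 2 × p + 30 | 0.70 | 0.83 | +74.1 | 78.2 | 0.5 |

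Both planned measures are identical in all three rows.

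**Check 4: can the missing quantity be estimated?** With 42 independent meals, one person's Fisher-z correlation has a standard error of 1/√39 = 0.16. Averaged over 300 people this is 0.16/√300 = 0.009. Exclusions will reduce the number of meals, but the mean within-person correlation should remain well estimated.

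**The case against.** Several points on the other side are sound and limit the claim.

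- **There are two measures, not one.** A reader might infer that accuracy rests on a single correlation. It does not, since the AUC is also fixed. The AUC shares both weaknesses, however, as Checks 1 and 3 show.
- **A carbohydrate benchmark is partly planned.** A reader might infer that there is none. The descriptive correlation of PPGR with meal carbohydrate, fat and protein is on the same scale as the model's r. It does not list calories, is not tied to the held-out participants and is not set against the model. What is missing is the head-to-head comparison.
- **Between-person prediction is a legitimate aim.** The study sets out to characterize interindividual variability, and the sample-size section speaks of prediction from individual characteristics. Pooled r is therefore relevant, though not sufficient for meal choice.
- **The extreme models are unlikely.** Meal content, timing and activity are among the features, and the meal schedule deliberately varies meals within a person, so zero within-person skill is a bound. Capturing all between-person variance in people the model has never seen is a further bound. A regressor fitted to PPGR and tested in the same study population is unlikely to be wrong twofold. The documents do not support a forecast that r *will* be inflated or the scale grossly wrong. Check 2 needs neither extreme.
- **The article is condensed.** Further metrics may stand in a full analysis plan, and the article does not say that only r will be reported. That would excuse silence, but here the article names the performance target and chooses the measures for it, and those measures do not match the target.
- **No decision rule depends on r.** The protocol sets no threshold, and no treatment in this observational cohort depends on it. The consequence is for the strength of the conclusion.

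**Conclusion.** The point holds in a bounded form. The two fixed measures are useful but, alone, support neither accurate prediction of individual responses nor the step to personalized diets. They cannot detect linear miscalibration, and they do not separate between-person from within-person skill.

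The size depends on an ICC that the article does not give. At an assumed 0.3-0.5, between-person knowledge alone could produce a pooled r of 0.39-0.50 (half captured) or 0.55-0.71 (all captured). At ICC 0.1 the ceiling is about 0.3. The conclusion is that pooled r *can* be sizeable without within-person skill; the documents do not show that it will be. The calibration figures illustrate what the measures miss, on a scale borrowed from nondiabetic people. The fault can be corrected in the analysis and should be; it does not affect the design or the data collected.

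**What to change.** Keep pooled r and the AUC, and define what is aggregated. On the held-out participants, add:

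1. the distribution of within-participant correlations between predicted and measured PPGR, with a prespecified minimum number of usable meals per participant;
2. MAE or RMSE in mg/dL·h;
3. calibration slope and intercept;
4. the same figures for a carbohydrate-only and a calorie-only model trained on the same training data, with differences from the main model and intervals from a bootstrap that resamples participants.

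State in advance that conclusions about accuracy rest on the error and calibration measures, and conclusions about personalization on the within-participant correlations and the gain over the simple models.

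The cost is small: the additions use predictions already produced plus two simple models, with no change to recruitment, sample size or data collection. The real downside is that reported performance may look less favourable than pooled r alone.
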